## Abstract

**Background:**

Timely detection of atrial fibrillation (AF) in implantable cardioverter defibrillator (ICD) patients is clinically important for prevention of AF-related complications and inappropriate shocks. Patients with coronary artery disease (CAD) and a dual or triple chamber ICD show a high incidence of device-detected AF. Whether CAD patients with a single chamber ICD carry a similar risk for device-detected AF remains unknown.

**Study design:**

The INDICO AF trial is an investigator-initiated, multicentre, observational study evaluating the incidence of subclinical AF (SCAF) in CAD patients who will receive a single chamber ICD as primary prevention for sudden cardiac death (SCD). Fifty patients will receive a single chamber ICD with an integrated RR interval based AF detection algorithm. In combination with remote monitoring, rhythm data will be collected monthly. The primary endpoint is the incidence of SCAF at 1 year of follow-up; secondary endpoints include time until 10 and 20% of the patients have a first episode of SCAF. All patients in whom SCAF is detected will be invited for an outpatient visit and will receive adequate anticoagulation treatment when appropriate according to the CHA2DS2-VASc score and current guidelines.

**Conclusion:**

The INDICO AF trial will quantify the incidence of SCAF in patients with an ICD and CAD. The study will underscore the clinical value of SCAF detection in single chamber ICD patients using remote patient monitoring and may improve patient care. This trial is registered at trialregister.nl with trial NTR6910.

## Background

The implantable cardioverter defibrillator (ICD) has shown to be successful in preventing sudden cardiac death (SCD) in patients with ischaemic and non-ischaemic cardiomyopathy, both as secondary or primary prevention. Currently, the European Society of Cardiology guidelines for the management of patients with ventricular arrhythmias and the prevention of SCD give a class IA recommendation for ICD implantation in patients with ischaemic cardiomyopathy with a reduced left ventricular ejection fraction (LVEF) ≤35% at least 6 weeks after myocardial infarction [1]. Besides protection against SCD, the monitoring capacities of the ICD may further improve patient care by timely detection of signs and determinants of deterioration.

Atrial fibrillation (AF) is the most common cardiac arrhythmia worldwide associated with a doubled mortality rate and a fivefold increase in ischaemic stroke even as independent risk factor [2]. Stroke prevention is therefore indicated in patients with an increased risk according to the CHA2DS2-VASc score [3]. The incidence and prevalence of AF are expected to further rise over the forthcoming years, partially due to ageing of the population and as a consequence of better survival of conditions that predispose to developing AF, such as heart failure and coronary artery disease (CAD). Indeed, the incidence of AF is considerably higher in patients with CAD and impaired left ventricular function.

Besides the increased risk of ischaemic stroke, AF in patients with ICDs has been associated with the occurrence of inappropriate shocks and is also a marker for worse prognosis [4]. Timely detection of AF in these patients is therefore of great clinical importance to prevent AF-associated complications.

The capability of conventional dual or triple chamber ICDs to detect subclinical AF (SCAF) has shown that the risk of SCAF in patients with CAD and a dual or triple chamber ICD is high [5]. It is likely that patients with CAD receiving a single chamber ICD for primary prevention of SCD carry a similarly high risk of SCAF, but so far, the incidence of SCAF in this patient population is unknown.

The newly developed and validated AF detection algorithm is incorporated into a single chamber ICD (VISIA AF™, Medtronic), and provides a platform to investigate incidence and prevalence of SCAF in single chamber ICD patients [6, 7]. This dedicated algorithm for AF detection reliably detects the presence or absence of AF. Detection of AF in patients with a reduced LVEF and CAD frequently has therapeutic implications, and delay of the diagnosis may negatively affect prognosis. The aim of the INDICO AF study, therefore, is to investigate the incidence of SCAF in a population of patients without AF, but with CAD and LVEF ≤35% undergoing ICD implantation for primary prevention of SCD.

## Study design

The INDICO AF trial is a multicentre observational study, conducted within four high volume ICD implantation centres in the Netherlands. Fifty patients with CAD and LVEF ≤35% will receive a single chamber ICD including an algorithm-based rhythm recorder (VISIA AF™, Medtronic). The primary endpoint of the study is the incidence of SCAF after 1 year of follow-up; secondary endpoints include the time until 10 and 20% of the patients have a first episode of SCAF. In combination with remote monitoring, data will be collected monthly, and follow-up will continue until 20% of patients have had a first event of SCAF. In addition, blood will be drawn during the 6 and 12 month follow-up visits. All patients in whom SCAF is detected will be invited to the outpatient clinic and will receive standard of care treatment, according to the CHA2DS2-VASc score and current guidelines [3]. The trial organisation is shown in Fig. 1.

**Fig. 1 Fig1:**
[figure not shown]
INDICO AF study flowchart. *ICD* implantable cardioverter-defibrillator, *CAD* coronary artery disease, *ECG* electrocardiogram, *AF* atrial fibrillation

### Primary and secondary endpoints

The initial hypothesis of this study is that patients with CAD and a primary indication for a single chamber ICD are at high risk for SCAF. The primary endpoint is the incidence of SCAF in single chamber ICD patients with CAD at 1 year. If this is less than 20% after 1 year, we will continue the study until 20% of patients have had a first episode of SCAF. Further secondary endpoints include the burden of SCAF, the occurrence of transient ischaemic attack (TIA), stroke or systemic embolism and the incidence of appropriate or inappropriate ICD therapy. All events will be adjudicated by an independent event committee, whose members are not investigators in the INDICO AF study.

To relate clinical characteristics of SCAF with biochemical changes, additional biomarkers will be sampled in the blood of patients included in this study. Specifically, analysis of biomarkers associated with myocardial fibrosis, inflammation, oxidative stress and heart failure will be assessed. In a prespecified sub-analysis, blood, ECG and ICD data in combination with the actual documentation of SCAF will be used to evaluate treatment decisions, and attempts will be made to construct a decision model guiding such treatment decisions.

### Patient selection

Patients with a class IA indication for ICD therapy as primary prevention for SCD and age between 65 and 80 years may be eligible for this study. Main exclusion criteria are current AF or a history of AF and the use of vitamin K antagonists or non-vitamin K antagonists (NOACs). Complete inclusion and exclusion criteria are shown in Tab. 1.

**Table 1 Tab1:** Inclusion and exclusion criteria

Inclusion	Exclusion
Age 65 ≥ 80 years	Current AF or a history of AF
CAD	Use of vitamin K antagonist or NOACs
LVEF ≤35%	Use of class I or III antiarrhythmic drugs
Life expectancy >2 years	Prosthetic heart valves
	Dilated or hypertrophic cardiomyopathy
	Congenital heart disease for which surgical correction was performed
	Inherited arrhythmia syndrome
	Active malignant disease
	A history of anthracycline use
	A history of TIA, stroke or systemic embolism
	Life expectancy <2 years

*CAD* coronary artery disease, *LVEF* left ventricular ejection fraction, *AF* atrial fibrillation, *NOAC* non-vitamin K oral anticoagulant, *TIA* transient ischaemic attack

### Device implantation and programming

Included patients will receive a single chamber ICD (VISIA AF™, Medtronic) with an integrated AF detection algorithm as part of standard of care ICD therapy. The VISIA AF™ is CE marked and commercially available in the Netherlands. It enables continuous monitoring for SCAF in single chamber ICD patients, by detecting RR interval based SCAF episodes of ≥6 min [6]. Episodes will be classified as SCAF at the end of the third 2‑min period of SCAF (Fig. 2b). The label of each 2‑min block is the result of a newly created Lorentz plot: a scatterplot of RR interval versus the preceding RR interval (Fig. 2a). As a standard setting, the ICD will only store the cumulative duration and the number of separate SCAF episodes. However, the ICD contains a dedicated Holter that communicates with the ICD and allows recording of the duration of individual AF episodes, thereby providing insight into the temporary distribution of AF episodes. The Holter monitor will only be enabled in patients in whom SCAF is detected during the study. All patients will be equipped with a remote monitoring system.

**Fig. 2 Fig2:**
[figure not shown]
**a** Lorenz plot of ∆RR intervals (−600 ms to +600 ms) during a 2-min block. *Left:* the dispersion of *dots* during a 2-min block labelled as AF by the device. *Right:* the dispersion of *dots* during a 2-min block labelled as NO AF by the device. **b** An episode is detected and stored as SCAF if there are three consecutive 2 min-blocks labelled as AF. *AF* atrial fobrillation, *SCAF* subclinical atrial fibrillation

### Follow-up

The occurrence of SCAF will be monitored via remote monitoring on a monthly basis as described previously [8, 9], for 1 year or until 20% of patients have had a first SCAF episode. All subjects will be followed at least until the last subject completes their 12-month follow-up visit. Patients will be seen at the outpatient clinic at 6 and 12 months for repeated blood testing and ECG.

### Sample size and power calculations

A total of 50 patients will be included. This sample size is powered for the primary endpoint, namely the incidence of SCAF in patients with CAD and a primary indication for a single chamber ICD. As this is an exploratory analysis, and data on the incidence of SCAF in patients with CAD and a reduced LVEF are inconclusive, we powered the study on an estimated incidence of AF of 8.3% in patients with CAD and a reduced LVEF without the use of a cardiovascular implantable electronic device (CIED) to detect AF, and an expected event rate of 20% of the primary endpoint detected by a CIED in a high-risk population [5, 10, 11]. Using a one-group, one-sided χ^2^ test, with a significance level of 0.05 alpha and 80% power, 46 patients would be required. Taking into consideration a loss of follow-up of approximately 10%, this would result in a total number of 50 subjects to be included. If the power is not achieved after 1 year, patients will be followed on an event-driven basis until 20% of patients demonstrate SCAF.

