### Clinical implication of device-detected AF

Of all strokes, 25% are of unknown cause and undiagnosed AF may be the aetiological factor [12]. Continuous monitoring of AF is superior to conventional follow-up visits or intermittent rhythm monitoring to identify AF after a cryptogenic stroke or detect AF recurrence after therapeutic interventions [9, 13]. In patients with a pacemaker, the incidence of SCAF is high and associated with an increased risk of stroke [14]. A relation between the duration of device-detected AF and stroke was demonstrated in a subanalysis of the ASSERT trial, although the event rate was lower than in patients with overt AF [15]. Not surprisingly, CIEDs with the ability to detect SCAF are of great interest to timely detect AF and prevent AF-related complications, as the population receiving ICD is generally older and has comorbidities increasing the risk for both AF and stroke. Indeed, the incidence of SCAF detected by an implantable loop recorder in patients without a history of AF but with a CHADS score ≥2 was 34% in 1 year [16].

Whether or not the implications with regard to oral anticoagulation are the same in patients with device-detected AHRE is subject of two ongoing clinical trials [17, 18]. There is no consensus either on whether AHRE detected from an atrial electrogram should be valued the same as SCAF detection based on irregularity of the RR intervals, or that stroke risk is merely driven by the duration of SCAF episodes [15]. Irrespective of whether anticoagulation should be started in all patients, establishing the diagnosis of AF is critical to determine increased stroke risk. This also applies for patients with an embolic stroke of undetermined source, as it was shown that starting rivaroxaban without documentation of AF in those patients was found to be futile compared with standard of care with aspirin [19].

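### The one-group test sets device-detected SCAF against an AF rate found without a device, so rejecting 8.3% does not by itself confirm high risk

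*Protocol article*

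**What the plan says.** Under Primary and secondary endpoints the article states its hypothesis: "patients with CAD and a primary indication for a single chamber ICD are at high risk for SCAF". What is measured first is the 1-year incidence of SCAF. Under Device implantation and programming, SCAF is an RR-interval-based episode of at least 6 minutes, found by continuous monitoring in the ICD.

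Sample size and power calculations contains the only inferential test in the article. The null rate is "an estimated incidence of AF of 8.3% in patients with CAD and a reduced LVEF without the use of a cardiovascular implantable electronic device". For the alternative, the section takes "an expected event rate of 20% of the primary endpoint detected by a CIED in a high-risk population". The test is a χ² test in one group, one-sided, and its requirement reads: "with a significance level of 0.05 alpha and 80% power, 46 patients would be required". After allowing for loss to follow-up, 50 are to be included. The same section calls the analysis exploratory, and the Summary calls the study a pilot.

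The conclusion of the abstract first says that the trial will quantify incidence, then adds: "The study will underscore the clinical value of SCAF detection in single chamber ICD patients".

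**The concern.** The two sides of the test measure different things. The null is AF found without an implanted device; the endpoint is SCAF found by one that monitors continuously. SCAF here is by definition a device finding, so a claim that its incidence is high needs a reference rate obtained by comparable detection, and a non-device rate cannot supply one.

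The article recognises that detection intensity matters. Under Clinical implication of device-detected AF it says: "Continuous monitoring of AF is superior to conventional follow-up visits or intermittent rhythm monitoring". That sentence goes on to limit itself to AF after cryptogenic stroke and recurrence after therapeutic interventions, so it does not give the size of the effect in this population. It does show that the direction of the problem is known.

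At stake is how a significant result is read. A p-value below 0.05 against 8.3% could be reported as confirming high risk when better detection alone might have produced it.

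**Working it through.** **Inputs** (Sample size and power calculations): p0 = 0.083, p1 = 0.20, one-sided alpha 0.05, power 0.80, 46 evaluable, 50 included. The detection ratios in step 3 are assumptions; the article gives none.

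**1. Reproducing the plan's figure.**

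n = [z(0.95)·√(p0(1−p0)) + z(0.80)·√(p1(1−p1))]² / (p1−p0)²

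= [1.645 × 0.2759 + 0.842 × 0.400]² / 0.117²

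= 0.6248 / 0.01369 = 45.64, rounded up to 46.

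This agrees with the stated 46.

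**2. What it takes to reject 8.3% with 46 patients.**

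- Asymptotic: the observed proportion must exceed 0.083 + 1.645 × √(0.083 × 0.917/46) = 0.083 + 1.645 × 0.0407 = 0.150. Six events give 13.0% and do not reject; 7 events (15.2%) do.
- Exact binomial: the smallest r with P(X ≥ r | 46, 0.083) ≤ 0.05 is 8 (17.4%), with tail probability 0.034. At r = 7 the tail is 0.084.

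**3. Rejection through detection alone.** Suppose the underlying risk equals the benchmark and the device finds k times as much AF, so the device-detected rate is 0.083k. The chance of rejection is P(X ≥ r | 46, 0.083k):

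| k (assumed) | device-detected rate | exact, r = 8 | asymptotic, r = 7 |
|---|---|---|---|
| 1.5 | 12.5% | 21% | 35% |
| 2 | 16.6% | 50% | 66% |
| 2.4 | 19.9% | 72% | 84% |
| 3 | 24.9% | 92% | 96% |

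The planning alternative is itself 0.20/0.083 = 2.4 times the null. A device that found 2.4 times as much AF in patients of unchanged risk would therefore reject about as often as the design intends to under its hypothesis (73% exact and 84% asymptotic at a true 20%).

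**4. What the estimate would say.** Exact (Clopper-Pearson) two-sided 95% intervals:

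- 9/45 (20%): 9.6 to 34.6%
- 10/50 (20%): 10.0 to 33.7%
- 8/46 (bare rejection by the exact test): 7.8 to 31.4%

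If the expected 20% is observed, the interval runs from just above the null to about the 34% in 1 year that the article quotes for loop recorders in patients with a CHADS score of at least 2. The interval shows this imprecision; a p-value against 8.3% hides it.

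**The case against.** The strongest reply is that the mismatch is disclosed and the aim is modest. The sample size section labels both rates by how they were detected and calls the analysis exploratory. The primary endpoint is already the 1-year incidence, and the abstract, Discussion and Summary speak of quantifying, estimating or evaluating it. The test appears only in the sample size section, and how the result will be reported may be settled in a full protocol or analysis plan that is not shown. All of this stands, and it limits the point to the inference drawn from the test. Disclosure and the exploratory label do not make a rejection of 8.3% informative about high risk.

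Two stronger readings are tempting, and the documents support neither.

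- A reader might infer that rejection would show a difference in detection method. It would not. This is a comparison of one group with an external rate, and case mix (for example age 65 to 80, no prior AF or stroke) and true risk may differ as well. Nor is rejection assured by better detection: at an assumed 1.5 times, the exact test rejects only 21% of the time.
- A reader might infer that the study tests similarity to patients with dual or triple chamber ICDs. That is an open question in the abstract and a likely expectation in the Background, not an endpoint or a planned test.

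Device-based comparators also have detection problems of their own. The Discussion says that loop recorders call AF on one 2-minute block, not three; that RR-based detection does not identify flutter or atrial tachycardia; and that atrial-lead rates may be overestimated. They can give context, but they do not make a clean replacement null.

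**Conclusion.** The concern holds in a limited form. The only stated test sets device-detected SCAF against AF found without a device, so rejecting 8.3% shows only that device-detected incidence exceeds 8.3%. It cannot separate high risk from more sensitive detection or different case mix, and it should not be read alone as confirming the hypothesis.

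The table in the working gives the size. It rests on 46 evaluable patients, on an underlying risk equal to the benchmark, and on assumed detection ratios that the article neither gives nor rules out. The 1-year incidence remains a valid estimate and can inform a judgement of high risk descriptively.

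**What to change.** - Base the primary conclusion on the 12-month SCAF incidence with an exact two-sided 95% confidence interval.
- Keep the 8.3% comparison as descriptive, and state that it is confounded by detection method and case mix.
- Set the estimate beside device-detected rates descriptively only, with the Discussion's own caveats on loop recorders and atrial-lead detection.
- In the abstract's conclusion, replace the sentence that announces clinical value in advance with one saying that the study quantifies incidence.

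No extra patients, visits or data are needed. The sponsor gives up a claim of statistical significance, and the sample size can stay at 50, justified by the width of the interval (10.0 to 33.7% if 10 of 50 have SCAF).

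### At 46 patients the chi-square approximation does not deliver 5% alpha and 80% power together; an exact binomial test has about 73% power

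*Protocol article*

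**What the plan says.** The section Sample size and power calculations of the protocol article sets the reference rate as "an estimated incidence of AF of 8.3% in patients with CAD and a reduced LVEF without the use of a cardiovascular implantable electronic device" and the alternative as "an expected event rate of 20% of the primary endpoint detected by a CIED in a high-risk population". The test is introduced with "Using a one-group, one-sided" and is a chi-square test. The result is "with a significance level of 0.05 alpha and 80% power, 46 patients would be required". Enrolment is then rounded up for attrition: "Taking into consideration a loss of follow-up of approximately 10%, this would result in a total number of 50 subjects to be included".

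The same section presents the sample size as powered for the primary endpoint, and also calls the analysis exploratory. Primary and secondary endpoints fixes that endpoint as SCAF incidence at 1 year. The Summary describes the study as small, observational and a pilot. The article mentions no exact test and no continuity correction.

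**The concern.** A one-sample chi-square test treats the event count as roughly normal under the null. Here the null count averages fewer than four events. Its distribution is skewed and lumpy, and moving the cut-off by one event shifts the tail probability by several percentage points. A sample size from the smooth formula can then state an alpha and a power that no actual cut-off achieves together.

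At stake is the truth of the operating characteristics stated for the primary endpoint. If the uncorrected chi-square rule were also used for inference, a finding above 8.3% could carry more than the stated 5% false-positive risk. If a valid exact test were used instead, the chance of detecting a true 20% would be below the stated 80%.

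**Working it through.** **Inputs**, all from Sample size and power calculations: p0 = 0.083, p1 = 0.20, one group, one-sided alpha 0.05, power 0.80, 46 evaluable, 50 enrolled, about 10% loss.

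**1. Reproduce the plan's figure.**

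n = {[z(0.95)·√(p0(1−p0)) + z(0.80)·√(p1(1−p1))] / (p1−p0)}²

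= {[1.645·√(0.083·0.917) + 0.842·√(0.20·0.80)] / 0.117}² = 45.64, which rounds up to 46.

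Approximate power at 46 is 80.2%. The stated 46 is reproduced. A continuity-corrected version of the formula gives 54, so the plan used the uncorrected form.

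**2. Expected null events.** 46 × 0.083 = 3.82. At 45 it is 3.74.

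**3. What the chi-square rule does at 46.** The critical count is 46·0.083 + 1.645·√(46·0.083·0.917) = 6.90, so it rejects from 7 events. With exact binomial tails:
- alpha = P(X ≥ 7 | 46, 0.083) = 8.4%
- power = P(X ≥ 7 | 46, 0.20) = 84.1%

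**4. What an exact level-0.05 test does at 46.** Seven events is too few (8.4%), so it rejects from 8:
- alpha = P(X ≥ 8 | 46, 0.083) = 3.4%
- power = P(X ≥ 8 | 46, 0.20) = 72.7%

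**5. The range from a 10% loss to no loss.**

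| Evaluable n | Chi-square rejects from | Alpha | Power | Exact test rejects from | Alpha | Power |
|---|---|---|---|---|---|---|
| 45 | 7 | 7.6% | 82.3% | 8 | 3.0% | 70.3% |
| 46 | 7 | 8.4% | 84.1% | 8 | 3.4% | 72.7% |
| 47 | 8 | 3.8% | 74.9% | 8 | 3.8% | 74.9% |
| 48 | 8 | 4.3% | 77.1% | 8 | 4.3% | 77.1% |
| 49 | 8 | 4.7% | 79.1% | 8 | 4.7% | 79.1% |
| 50 | 8 | 5.2% | 81.0% | 9 | 2.1% | 69.3% |

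No row has alpha at or below 5% and power at or above 80%. The closest are 49 (4.7%, 79.1%) and, for the chi-square rule, 50 (5.2%, 81.0%). The smallest n that meets both exactly is 56 (reject from 9, alpha 4.0%, power 81.5%).

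**6. Attrition.** Keeping 46 after a 10% loss needs 46/0.90 = 51.1, so 52 enrolled. With 50 enrolled, keeping 46 allows (50−46)/50 = 8% loss; a full 10% loss leaves 45.

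**The case against.** The strongest defence is that nothing was miscalculated. The article names a large-sample test, and that test gives 46. This stands: the fault lies in the approximation, and a reader who inferred an arithmetic slip would be wrong.

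A reader might also infer that the trial's test breaks its error rate at most plausible final sizes. The table does not support that. The chi-square rule exceeds 5% at three of the six sizes (45, 46 and 50), at 50 by only about a quarter of a point. At 47 to 49 it coincides with the exact test.

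Nor does the article say that the chi-square test will be the final analysis. The test appears only in the sample-size paragraph, the endpoint is an incidence, and no decision is tied to rejecting 8.3%. The full protocol or SAP may name an exact test. That would settle the alpha question, but power at 46 would then be 73%, so the 80% would still be wrong.

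The exploratory and pilot framing lowers the urgency but does not make a stated power true. The provision to extend follow-up when power is not achieved does not help either: the primary endpoint is incidence at 1 year, and later events do not add power to a 1-year comparison.

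On attrition, the article says approximately 10%, and 8% fits that wording. This is a refinement only.

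**Conclusion.** The point holds at moderate severity. The 46 is right for the formula named, but at 46 patients alpha of 5% and power of 80% are not available together: either alpha is 8.4% with 84% power, or alpha is 3.4% with 72.7% power. Over 45 to 50 evaluable patients the exact test has 69–79% power, a shortfall of about 1 to 11 points against the stated 80%. Power is not monotone: full retention of 50 moves the cut-off to 9 events and gives 69.3%, slightly below the 70.3% at 45.

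The figures assume 8.3% is a fixed reference value, a true 1-year rate of 20%, independent patients, and a simple proportion among evaluable patients.

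A reader might conclude that the trial must enrol more. The documents do not support that for a study described as exploratory and a pilot; an accurate power statement is enough.

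**What to change.** In Sample size and power calculations:
- Name the exact one-sided binomial test against 8.3%, rejecting from 8 events at 45 to 49 evaluable patients and from 9 at 50. The cut-offs may equally go in the SAP.
- Replace the 80% claim with about 69–79% power over 45 to 50 evaluable patients: 70% at 45, 73% at 46, 79% at 49 and 69% at 50. State that 46 came from a large-sample approximation.
- As a minor clarification, say that 50 enrolled allows 8% loss to keep 46, and that a full 10% loss leaves 45.

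The cost is a change of wording and a less favourable power figure. Enrolment, follow-up and data collection do not change.

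### The extension to 20% SCAF is written as a remedy for unachieved power, which it cannot be; the test against 8.3% should be confined to 12-month data

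*Protocol article*

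**What the plan says.** All references are to the protocol article. The abstract, Study design, and Primary and secondary endpoints all define the primary endpoint as SCAF incidence at 1 year. The abstract and Study design name the time until 10% and 20% of patients have a first episode as secondary endpoints.

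Sample size and power calculations gives the comparison behind the sample size. The reference is 8.3% without a device ("we powered the study on an estimated incidence of AF of 8.3% in patients with CAD and a reduced LVEF without the use of" a cardiac implantable device) and the alternative is "an expected event rate of 20% of the primary endpoint detected by a CIED in a high-risk population". The test is described as follows: "Using a one-group, one-sided χ^2^ test", "with a significance level of 0.05 alpha and 80% power, 46 patients would be required". Allowance for loss to follow-up brings the total to 50. The paragraph then closes with "If the power is not achieved after 1 year, patients will be followed on an event-driven basis until 20% of patients demonstrate SCAF".

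The extension appears elsewhere with a different trigger or none. Primary and secondary endpoints says "If this is less than 20% after 1 year, we will continue the study until 20% of patients" have had an episode. Study design says simply that "follow-up will continue until 20% of patients have had a first event of SCAF". The article states no maximum duration, and no section says whether the test against 8.3% uses the 1-year data or the data at the end of the extension.

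**The concern.** In a one-group test of a proportion, power is set by the sample size, the null, the alternative and alpha. It is not a quantity that is found lacking at 1 year and then made up by waiting. The extension stops on the outcome itself, at a proportion equal to the assumed alternative. A proportion obtained in this way says how long it took to reach 20%, not how high the incidence is.

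The rule closes the paragraph that justifies the primary comparison and is offered as its remedy. An analyst who follows that sentence could test the end-of-extension proportion against 8.3%. The result would then follow from the stopping rule, and a cohort with exactly the reference incidence could be reported as high risk. The article describes the study as a pilot for larger trials, so such a conclusion could carry forward.

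**Working it through.** **Inputs from the article:** p0 = 0.083, p1 = 0.20, one-sided alpha 0.05, power 80%, 46 evaluable, 50 enrolled, stop at 20% (10 of 50).

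**1. The stated sample size.** n = [1.645·√(0.083·0.917) + 0.842·√(0.20·0.80)]² / (0.117)² = 45.64, rounded up to 46. The figure reproduces. Going from 46 to 50 implies 8% loss, compatible with approximately 10%. The sample size is not in error.

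**2. Rejection boundary at n = 50.** The standard error under the null is √(0.083·0.917/50) = 0.0390.

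| Events | Proportion | z | Chi-square, one-sided 0.05 |
|---|---|---|---|
| 7 | 14% | 1.46 | does not reject |
| 8 | 16% | 1.97 | rejects |
| 9 | 18% | 2.49 | rejects |
| 10 | 20% | 3.00 | rejects (p = 0.0014; exact p = 0.007) |

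The exact binomial test rejects from 9 events. The stopping target of 10 is above both boundaries.

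**3. Fixed 1-year test.** Chi-square (8 or more events): P(X ≥ 8) is 5.2% at 8.3% and 81% at 20%. Exact test (9 or more): 2.1% and 69%. Nothing is predetermined here.

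**4. How often the extension starts.** It starts when fewer than 10 of 50 have SCAF at 1 year: 99.3% of trials at a true 8.3%, and 44% at a true 20%.

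**5. If the test were made at the end of the extension.** Assume that 8.3% is an annual rate (the article gives no time window), that the hazard is constant, and that there is no death or loss. The cumulative incidence at year T is 1 − 0.917^T, and the chance of a positive test is P(X ≥ 10) for n = 50:

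| Year | Cumulative incidence | P(at least 10 of 50) |
|---|---|---|
| 1 | 8.3% | 0.7% |
| 2 | 15.9% | 27% |
| 3 | 22.9% | 74% |
| 4 | 29.3% | 95% |
| 5 | 35.2% | 99% |

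The cumulative incidence passes 20% at ln(0.80)/ln(0.917) = 2.6 years.

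**6. Sensitivity.**
- Lower true incidence, no loss: at 4% a year, 10 of 50 is reached in 45% of trials by year 5 and 99% by year 10. At 2% a year, it is 2% and 43%.
- Assumed 10% yearly death or loss (simulation): at 8.3% a year, 17% by year 2, 54% by year 3 and 92% by year 5. At 2% a year, 28% even with unlimited follow-up.

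**7. The two triggers.** With 8 or 9 of 50 at 1 year, the planned chi-square test has already rejected, yet the observed incidence is below 20%, so Primary and secondary endpoints still extends. At a true 20% the chance of this is P(X ≥ 8) − P(X ≥ 10) = 0.810 − 0.556 = 25%.

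**The case against.** The strongest reply is that the primary endpoint is consistently set at 1 year and the extension has a purpose of its own. Time to 20% is a named secondary endpoint and cannot be observed without following patients that far. In Primary and secondary endpoints, the sentence after the extension goes on to further secondary endpoints, which suggests that the extension belongs among them. The choice of dataset for a test may also be settled in an analysis plan that is not shown, and the study calls itself exploratory and small.

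Most of this stands, and it rules out a stronger reading. A reader might infer that the rule forces the observed proportion to 20% and guarantees a positive result whatever the true incidence. The documents do not support that:
- No section says that the 8.3% test is run or repeated on extended data.
- The proportion is held at 20% only if the 1-year value is below it.
- At low incidence, or with competing death or loss, 20% may not be reached in any practical time.

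The year-by-year figures also need a time window for 8.3% that the article does not give. If 8.3% covers more than one year, they fall.

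The power sentence itself does not survive. It is not detail left to an analysis plan. The article states a rationale, and the rationale is statistically invalid.

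**Conclusion.** The point holds in a limited form. Extending follow-up until 20% have SCAF cannot supply missing power for the primary comparison, and the sentence that says so is wrong as written. A test on 1-year data is sound. A test at the end of the extension would reject whenever 20% is reached, because 10 of 50 lies above the boundary.

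For a cohort at the null rate, the chance of such a rejection rises from 27% by year 2 to 99% by year 5, against 5.2% for the 1-year chi-square test. This rests on an annual 8.3%, constant hazard and no death or loss; with lower incidence or with loss it is smaller, in some cases much smaller. The two triggers for extension also disagree with each other and with the test's own boundary. The sample size of 46 is unaffected.

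**What to change.** In Primary and secondary endpoints and in Sample size and power calculations:

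- State that the primary estimate, with its confidence interval, and the test against 8.3% use first SCAF within 12 months only and are final whatever the result.
- Delete the clause that makes unachieved power the trigger for extension.
- Keep the extension solely for the secondary time-to-10% and time-to-20% endpoints.
- State that the proportion at the end of the extension is not compared with 8.3%.

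The cost is wording in the protocol and analysis plan, with no more patients. The sponsor must accept that a 1-year result below the rejection boundary is reported as such.
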